**Fig. 6 Fig6:**
[figure not shown]
Three-dimensional posture parameters measured by the GPS device. The postural parameters of the head in relation to the thoracic region: Postural translation A1 (Tz), A2 (Tx) measured in centimetres. Postural rotations B1 (RZ), B2 (Ry), B3 (Rx) measured in degrees

### Postural translations of the head

Tx (right or left side shifting or lateral translation): measure horizontal distance from the ideal plumb line passing through middle sternal notch to vertical line passing through nose.Tz (anterior or posterior translation): measure horizontal distance from the vertical line crossing the middle acromion process to the vertical line crossing the external ear.

### Postural rotations of head

Rx (flexion or extension position): measure angle between tragus of ear, canthus of eye and the horizontal line.Ry (right or left rotation): measure angle between glabella of forehead or tip of nose, the middle point of chin and the vertical line.RZ (right or left side bending): measure angle between the inferior margins of the right and the left ear and the horizontal line.

The time frame is pretreatment, post-treatment 10 weeks and after 3 months of follow-up.

### Withdrawal and dropout

All patients will have the right to withdraw from the study at any time. Participation will be terminated at any stage if the patient refuses to continue, withdraws their consent or violates the inclusion or exclusion criteria or the trial protocol. The trial will be terminated if the principal investigator believes that there are unacceptable risks of serious adverse events.

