**Methods/design:**

This pilot, single-blind, randomized controlled trial will divide 24 patients into two groups (study and control) using block randomization. Both groups will receive conventional treatment consisting of a moist hot pack, soft tissue mobilization, manual therapy and therapeutic exercise. The study group will undergo ambulatory mirror-image functional re-training wearing a 3D adjustable CTPCO. The primary outcome is feasibility, including recruitment (e.g., time to complete enrolment, recruitment rate), patient retention and adherence to treatment allocation (e.g., session attendance, home practice, use of non-study treatments). The secondary outcomes used to assess the effectiveness of the treatment will include neck pain (measures using the visual analogue scale (VAS)) and neck disability (measures using the neck disability index (NDI)), among other outcome measures, compared between the experimental and control groups. Three-dimensional posture parameters of head measurements will be provided by a Global Posture System (GPS). The outcome measures for determining the treatment effect will be assessed at three intervals: pre-treatment, after 10 weeks of intervention and after 3 months at follow-up.

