### Exclusion criteria

If patient report any of the following conditions:Neck pain associated with whiplash injuries, medical red flag history (such as tumour, fracture, metabolic diseases, rheumatoid arthritis and osteoporosis) [27].Neck pain with cervical radiculopathy or neck pain associated with externalized cervical disc herniation [27]Fibromyalgia syndrome; to avoid the similarity of fibromyalgia with a NSNP diagnosis, a physician will use the criteria for the clinical diagnosis of fibromyalgia according to the American College of Rheumatology [29]If the patient had previous surgery in the neck area (irrespective of the reason for the operation) [27]Neck pain accompanied by vertigo caused by vertebra basilar insufficiency or accompanied by non-cervicogenic headaches [27]People will also be excluded if they are undergoing any type of pain treatment or they have psychiatric disorders or other problems that contraindicate the use of the techniques in this study [27]If patient has true leg length discrepancy and an associated pathology of upper and lower limbs that may interfere with the global posture (e.g., foot, knee or hip deformities)The patients will be unable to attend a 10-week treatment programme and follow-up assessments after 3 months

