### Recruitment and retention

Recruitment and retention data include procedures for patient enrolment (goal of at least 80% of eligible patients accepting to be enrolled), patient adherence to the intervention (goal of at least 80% of patients attending 75% of treatment sessions and completing 75% of the prescribed exercises) and patient losses to follow-up (goal of at least 80% of participants completing the follow-up) [36].

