### Sample-size calculation

The sample size of a future, fully powered study will be estimated using sample-size calculations using the effect-size data from this pilot study. We will recruit 24 patients for two groups [37].

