### Statistical analysis

Results of primary outcome measures will be provided descriptively in tables and compared to the a priori established goals. To provide a recommendation for estimated sample size for a future full-scale RCT, between-group effect sizes and 95% confidence intervals (CIs) with Hedges correction will be calculated for changes in the secondary outcomes of VAS, NDI and 3D posture parameters. The mean ± standard deviation score for each of the subscales will be used in the calculation of the effect size. Estimated sample size will be determined using the between-subject effect size, with a minimum of 80% power (*α* = 0.05). The sample size will be increased to allow for an estimated 20% dropout rate. Statistical methods for the secondary outcome measures will be evaluated via comparisons of changes between groups. Complete case analyses will be performed to include outcomes from all patients who completed baseline and follow-up evaluations, as recommended in the Consolidated Standards of Reporting Trials (CONSORT) guidelines [39]. The between-group difference in change scores for each outcome measure from baseline to follow-up will be determined and reported as the means and 95% CI, using an analysis of covariance. Covariates of age and sex will be included in the analysis. All statistical analyses will be performed in SPSS version 23.0 software (IBM Corporation, Armonk, NY) with significance set at *P* < 0.05.

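### Ending participation for any protocol violation, combined with a complete-case analysis, can remove randomised patients for the behaviour the feasibility outcomes should measure, and may bias the pilot effect size

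*Protocol article*

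**What the plan says.** **Termination.** Under Withdrawal and dropout, participation ends at any stage if the patient refuses to continue, withdraws consent, or "violates the inclusion or exclusion criteria or the trial protocol". A violation is not defined, the rule is not limited to safety, and nothing says that such patients are still assessed.

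**Analysis set.** Statistical analysis states: "Complete case analyses will be performed to include outcomes from all patients who completed baseline and follow-up evaluations". No other analysis set is named.

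**Primary outcome.** The outcome is feasibility. The Abstract includes "adherence to treatment allocation (e.g., session attendance, home practice, use of non-study treatments" among its components. Recruitment and retention sets an adherence target ("goal of at least 80% of patients attending 75% of treatment sessions and completing 75% of the prescribed exercises") and, separately, a retention target ("goal of at least 80% of participants completing the follow-up").

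**Eligibility.** Being able to continue for 10 weeks and attend the 3-month follow-up is an inclusion criterion, and being unable to attend is an exclusion criterion. The exclusion criteria also state: "People will also be excluded if they are undergoing any type of pain treatment".

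**Use of the effect size.** It helps to select the primary outcome of the full trial (Primary outcome measure) and sizes that trial (Sample-size calculation; Statistical analysis).

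**The concern.** A feasibility trial has to observe patients who miss sessions, skip home exercise or seek other treatment. Here the same events can be read as grounds for ending participation. A patient who starts outside pain treatment meets an exclusion criterion and also supplies an adherence outcome. A patient who becomes unable to attend breaches an eligibility condition and also supplies attendance data.

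Two things are at stake. First, adherence and retention may no longer be separate measures: a terminated non-adherer becomes a retention failure by the trial's own act, and may or may not stay in the adherence denominator. Second, a patient terminated before the follow-up evaluation drops out of the complete-case comparison. The study arm alone has 30 treadmill sessions of 20 minutes in the orthosis, so its patients have more ways to depart from the protocol and removal may be unequal.

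**Working it through.** **Inputs from the protocol.** 24 patients ("We will recruit 24 patients for two groups"); goals of 80% for adherence and for retention; 80% power, α = 0.05 and a 20% dropout allowance for the future trial.

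**Inputs assumed.** Two-sided testing (sidedness is not stated); a true standardised difference of 0.50; removal rates; and the correlation ρ between the tendency to be removed and the change score. The 24 rests on a citation, with no effect size or SD, so it cannot be reproduced; it is not disputed here.

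**1. Retention.** 0.80 × 24 = 19.2, so 20 must complete and at most 4 may be lost. The binomial probability of at least 20 of 24 is:

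| True retention | P(goal met) |
|---|---|
| 90% | 0.915 |
| 85% | 0.713 |
| 80% | 0.460 |
| 75% | 0.247 |

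A few terminations can therefore decide the result.

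**2. Adherence.** Suppose 17 patients meet the adherence threshold and 4 others are terminated.
- All randomised: 17/24 = 70.8%, goal missed.
- Those remaining: 17/(24 − 4) = 17/20 = 85.0%, goal met.

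**3. Effect size.** Let the fraction p with the lowest latent score be removed from an arm, with standard normal change scores. The mean of those kept rises by ρλ, where λ = φ(z_p)/(1 − p) and z_p is the p-th normal quantile. Their variance becomes 1 − ρ²λ(λ − z_p).
- p = 0.30: λ = 0.497. p = 0.10: λ = 0.195. Difference 0.302.
- Pooled SD of those kept (30% removed in one arm, 10% in the other): 0.982 at ρ = 0.3; 0.926 at ρ = 0.6.
- Apparent difference = (true difference ± 0.302ρ)/pooled SD, plus when the study arm loses more.
- Per-arm size of the future trial = 2(1.96 + 0.8416)²/d² = 15.70/d², rounded up from unrounded d.

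| Removed, study vs control | ρ | True 0: apparent | True 0.50: apparent | Future n per arm |
|---|---|---|---|---|
| none | – | 0 | 0.50 | 63 |
| 30% vs 10% | 0.3 | 0.09 | 0.60 | 44 |
| 30% vs 10% | 0.6 | 0.20 | 0.74 | 30 |
| 10% vs 30% | 0.3 | −0.09 | 0.42 | 91 |
| 10% vs 30% | 0.6 | −0.20 | 0.34 | 133 |

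Equal removal of 10% or 20% in both arms gives no bias when there is no true effect, and 0.51 to 0.54 when the true value is 0.50. With ρ = 0 there is no bias. A simulation with 2,000,000 patients per arm agrees for the equal-removal and 30% vs 10% rows to about 0.01.

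The 20% dropout allowance does not correct this. It turns 2 × 63 = 126 into 126/0.8 = 157.5, so 158: it restores numbers, not a distorted effect size.

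**The case against.** The strongest reply is that a violation is undefined, and that the adherence goal itself presupposes patients below the threshold who are still counted. On that reading ordinary non-adherence is observed and does not lead to removal. This is a fair reading, but the termination rule as worded does not secure it, and the eligibility criteria on attendance and pain treatment pull the other way. The sections need reconciling.

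Several stronger readings are tempting and are not supported:
- **That the analysis is per-protocol in effect.** The complete-case sentence has no adherence condition; a non-adherent patient who attends assessment is analysed. Nothing says that data already collected are deleted.
- **That the effect estimate is biased, and optimistic.** The calculation shows a structural risk that vanishes when removal is unrelated to outcome and reverses when controls are removed more often.
- **That the effect would double.** Suppose 3 of 12 orthosis patients are removed, the other 9 gain 2 cm on VAS and controls gain 1 cm. If the 3 gained 0 cm, the difference as randomised is (9×2 + 3×0)/12 − 1 = 0.5 against 1.0 cm among those kept. Both arms receive the same conventional treatment, though; if the 3 gained 1 cm like controls, it is (9×2 + 3×1)/12 − 1 = 0.75 against 1.0. All these values are assumed.
- **That a patient with 10-week but no 3-month data is dropped.** This is possible under the wording but not stated.

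Two further points stand. Effect size is a secondary aim, and its precision is poor: with an assumed 12 per arm and d = 0.5, the 95% half-width is 1.96 × √(2/12 + 0.25/48) ≈ 0.81, larger than the shifts of 0.10 to 0.24 when the study arm loses more. Also, nothing in the text removes terminated patients from the adherence denominator; it is simply not fixed, and a fuller plan may fix it.

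**Conclusion.** The point holds in limited form. The firmer part concerns the primary outcome: the termination rule, read as written, can act on patients because of the behaviour that adherence and retention are meant to record. Five such terminations fail the retention goal, and in the example the adherence result moves between 70.8% and 85.0% on the denominator alone.

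The part about the treatment effect is a risk of unknown size and direction. Under assumed removal of 30% versus 10% and a true difference of 0.50, the estimate would be 0.60 to 0.74 and the future trial would have 44 to 30 per arm instead of 63; the mirror-image assumption gives the opposite error. The extra sessions in the orthosis arm make inflation plausible, not established. No figure stated in the protocol is shown to be wrong.

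The article gives recruitment as ongoing, and follow-up that is not collected cannot be recovered later, so an inexpensive clarification is worth making now.

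**What to change.** - **Withdrawal and dropout.** Reconcile this section with the Abstract and with Recruitment and retention, so that a protocol deviation does not end outcome assessment. Unless consent is withdrawn, invite the patient to the 10-week and 3-month assessments already in Table 1. When treatment itself should stop is a clinical matter not judged here.
- **Recruitment and retention.** State that all randomised patients are in the adherence and retention denominators.
- **Statistical analysis.** Analyse all randomised patients in their allocated arm using every available post-baseline value, for example with a mixed model adjusted for the baseline outcome. Keep complete case as a sensitivity analysis.

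The model does not replace continued follow-up: a patient with no post-baseline value contributes no outcome to it, and it stays biased if loss depends on unobserved response.

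The cost is revised wording, a few more follow-up contacts at visits already scheduled, and slightly more analysis work.

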### Statistical analysis

Results of primary outcome measures will be provided descriptively in tables and compared to the a priori established goals. To provide a recommendation for estimated sample size for a future full-scale RCT, between-group effect sizes and 95% confidence intervals (CIs) with Hedges correction will be calculated for changes in the secondary outcomes of VAS, NDI and 3D posture parameters. The mean ± standard deviation score for each of the subscales will be used in the calculation of the effect size. Estimated sample size will be determined using the between-subject effect size, with a minimum of 80% power (*α* = 0.05). The sample size will be increased to allow for an estimated 20% dropout rate. Statistical methods for the secondary outcome measures will be evaluated via comparisons of changes between groups. Complete case analyses will be performed to include outcomes from all patients who completed baseline and follow-up evaluations, as recommended in the Consolidated Standards of Reporting Trials (CONSORT) guidelines [39]. The between-group difference in change scores for each outcome measure from baseline to follow-up will be determined and reported as the means and 95% CI, using an analysis of covariance. Covariates of age and sex will be included in the analysis. All statistical analyses will be performed in SPSS version 23.0 software (IBM Corporation, Armonk, NY) with significance set at *P* < 0.05.

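### The 80% adherence and retention goals are judged on raw proportions in 24 patients with no stated interval, so a bare pass and a bare miss are nearly the same evidence

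*Protocol article*

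**What the plan says.** The protocol article makes feasibility the primary outcome. Under Recruitment and retention it sets three numerical goals:

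- Enrolment: "goal of at least 80% of eligible patients accepting to be enrolled".
- Adherence: "goal of at least 80% of patients attending 75% of treatment sessions and completing 75% of the prescribed exercises".
- Retention: "goal of at least 80% of participants completing the follow-up".

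The size of the pilot is given under Sample-size calculation: "We will recruit 24 patients for two groups". It is supported by a citation, with no precision argument.

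The Statistical analysis section states how the goals are used: "Results of primary outcome measures will be provided descriptively in tables and compared to the a priori established goals". The same section plans 95% confidence intervals for the between-group effect sizes and for the differences in change scores, all of which are secondary outcomes. It mentions no interval for the feasibility proportions. On the sample size of the later full-scale trial it adds: "The sample size will be increased to allow for an estimated 20% dropout rate".

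**The concern.** The pilot exists to inform a decision about a larger trial, and the 80% goals are its only numerical benchmarks for that decision. A proportion from 24 patients is imprecise. If it is set beside a fixed goal without an interval, the reader sees that the goal was met or missed but not how little the data say about the true rate. One patient moves the result from 79.2% to 83.3%, across the goal, on almost unchanged evidence. A table entry of 20/24, goal met, could be taken to show 80% retention when much lower rates remain compatible with the data. An entry of 19/24, goal missed, could be taken as a failure when rates well above 80% remain compatible. The secondary outcomes get a measure of precision and the primary outcome, as described, does not.

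**Working it through.** **Inputs.** n = 24 (Sample-size calculation). Goal 80% for adherence and for retention (Recruitment and retention). Dropout of 20% for the future trial (Statistical analysis), which corresponds to 80% retention. The number 24 cannot be reproduced, because the article gives no inputs for it.

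**Count needed.** 0.80 × 24 = 19.2, so at least 20 patients. 19/24 = 79.2% misses; 20/24 = 83.3% meets. At most 4 patients may be lost.

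**Chance of meeting one goal.** With X ~ Binomial(24, p), P(met) = P(X ≥ 20) = Σ C(24,k) p^k (1−p)^(24−k) for k = 20 to 24. At p = 0.80 the five terms are 0.196 + 0.149 + 0.081 + 0.028 + 0.005, which sum to 0.460 before rounding of the terms. Across true rates:

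| True rate | P(goal met) |
|---|---|
| 70% | 0.111 |
| 75% | 0.247 |
| 80% | 0.460 |
| 85% | 0.713 |
| 90% | 0.915 |
| 95% | 0.994 |

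If 79.2% were rounded up and counted as meeting the goal, the figure at a true 80% would be 0.656.

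**Exact 95% intervals.** The Clopper-Pearson lower limit is the 0.025 quantile of Beta(x, n−x+1). The upper limit is the 0.975 quantile of Beta(x+1, n−x).

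| Observed | Proportion | Exact 95% CI |
|---|---|---|
| 17/24 | 70.8% | 48.9% to 87.4% |
| 19/24 | 79.2% | 57.8% to 92.9% |
| 20/24 | 83.3% | 62.6% to 95.3% |
| 22/24 | 91.7% | 73.0% to 99.0% |
| 23/24 | 95.8% | 78.9% to 99.9% |
| 24/24 | 100% | 85.8% to 100% |

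The intervals for 19 and 20 are about 35 and 33 percentage points wide and share the range 62.6% to 92.9%. Every result from 17 to 23 leaves 80% inside its interval; only 24/24 has a lower limit above 80%.

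**Enrolment goal.** Its denominator is eligible patients, not 24. With 24 enrolled, the goal is met if at most 24 / 0.80 = 30 were eligible. The counts above do not apply to it, but the lack of a stated interval does.

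**The case against.** The strongest reply is that the article sets goals, not a pass/fail rule. Feasibility is also judged on interviews about protocol integrity, completeness of outcome data and success of assessor blinding. A descriptive report does not exclude intervals, and a condensed article may leave them to an analysis plan that is not shown. Much of this stands: the point improves a stated method and does not correct an error. What remains is that the article does say how the primary proportions will be judged, and mentions intervals only for other outcomes.

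A reader might go further than the documents allow in four ways.

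- *That the near-even odds at a true 80% show 24 patients to be too few.* They do not. Any cut-off gives roughly even odds when the truth lies on it: the chance is 0.58 with 50 patients and 0.56 with 100. That it falls below one half here comes from rounding 19.2 up to 20; with 25 patients, where 20 also suffice, it is 0.62.
- *That the pilot itself expects 20% dropout.* The figure belongs to the calculation introduced by "To provide a recommendation for estimated sample size for a future full-scale RCT". No retention rate is assumed for the pilot.
- *That missing one goal means the trial is declared not feasible, or that the goals must be met jointly.* No such rule is stated, so no joint probability can be attached to the plan.
- *That the comparison cannot tell good feasibility from bad.* It separates 70% from 90% well. The weakness lies between about 75% and 85%.

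**Conclusion.** The concern holds in a limited form. Comparing raw proportions in 24 patients with an 80% goal, with no stated interval, gives opposite results for 19 and 20 patients on nearly the same evidence. It discriminates poorly between true rates of 75% and 85%: a true 75% meets the goal one time in four, and a true 85% misses it 29% of the time (1 − 0.713 = 0.287). The size that matters is the interval of roughly a third of the scale around a result close to the goal.

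The figures assume that all 24 randomised patients form the denominator for adherence and retention, that patients are independent with a common rate, and that 79.2% is not rounded up to 80%. The true rates are illustrative. 80% is singled out because it is the goal and the complement of the dropout planned for the full-scale trial. The point does not invalidate the pilot or call for a larger one; it is a worthwhile and nearly free improvement to how the primary outcome is reported.

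**What to change.** In the Statistical analysis section:

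1. Report each primary feasibility proportion, with its own denominator, with an exact (Clopper-Pearson) 95% CI.
2. Say that the comparison with each goal will be interpreted in the light of that interval.
3. State that meeting or missing a goal with 24 patients does not by itself establish that the true rate is above or below 80%.

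Graded progression bands, expressed as counts of 24, are optional and their edges are the sponsor's choice. They soften the consequence of a one-patient difference but do not remove the imprecision, so they do not replace the intervals.

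The cost is a few sentences and one column in the feasibility table, with no extra patients or data. The article reports recruitment as ongoing. If that is still so, the wording can be fixed before results are known. The downside is a less clear-cut claim of feasibility.

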### Interventions

Twenty-four patients will be randomized into two groups (study and control) using block randomization. Both groups will receive conventional treatment consisting of a moist hot pack, soft tissue mobilization, manual therapy and therapeutic exercises.

The study group will also undergo ambulatory mirror-image functional re-training via the wearing of a 3D adjustable CTPCO. Patients in both groups will attend 30 physical therapy treatment sessions over a 10-week period at three sessions per week and then follow-up after 3 months. Short-term follow-up evaluations will be performed after 10 weeks of interventions, and the long-term follow up will be performed 3 months after the end of the 10 weeks of treatment. The flow diagram for this trial is presented in Fig. 1.

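### Sizing the full-scale trial from the effect size observed in 24 patients does not deliver the stated minimum of 80% power

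*Protocol article*

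**What the plan says.** Two places in the protocol article fix the rule. Under *Sample-size calculation*, listed among the primary (feasibility) outcomes, the size of a future study described as fully powered "will be estimated using sample-size calculations using the effect-size data from this pilot study". The same paragraph gives the pilot's size: "We will recruit 24 patients for two groups".

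Under *Statistical analysis*, "between-group effect sizes and 95% confidence intervals (CIs) with Hedges correction will be calculated for changes in the secondary outcomes", and then "Estimated sample size will be determined using the between-subject effect size, with a minimum of 80% power" at alpha 0.05. The result is increased for an estimated 20% dropout. The inputs are the pilot's own summary statistics: "The mean ± standard deviation score for each of the subscales will be used in the calculation of the effect size". The pilot analysis uses complete cases.

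The confidence intervals are calculated, but the sizing sentence does not use them. The minimal important change appears only under *Primary outcome measure*, as a threshold that the observed difference must pass before an outcome is nominated. It is not the difference to be powered for.

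**The concern.** A sample-size formula gives its nominal power only if the planning value is right. Here the planning value is an estimate from about 12 patients per arm. Required n varies with the inverse square of the effect size, so the two directions of error do not cancel. An overestimate shrinks the trial sharply, while an underestimate only adds power above 80%, which is capped at 100%.

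Neither named adjustment addresses this. The Hedges correction removes small-sample bias, not sampling variance. The dropout allowance replaces lost patients and adds no margin for uncertainty in the effect.

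The problem does not come from choosing among outcomes: it is present with a single outcome named in advance. The sample-size estimate is one of the pilot's listed feasibility products. A later trial that adopted it unchanged would be more likely than planned to miss a real effect.

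**Working it through.** **Inputs.** From the article: 24 patients in two groups, 80% power, alpha 0.05 ("with significance set at *P* < 0.05"), Hedges-corrected effect size, 20% dropout. Assumed, because the article does not state them: 1:1 allocation (12 per arm), a two-sided test, normal outcomes, and true d between 0.3 and 0.8. One outcome is fixed in advance, a trial follows whenever the observed g is above 0, and the dropout allowance offsets dropout exactly. The age and sex covariates are not modelled.

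**1. The nominal figure.** n per arm = 2(1.96 + 0.84)²/g² ≈ 15.70/g². Power by normal approximation = Φ(d√(n/2) − 1.96).
- g = d = 0.5: 15.70/0.25 = 62.8, so 63 per arm. Power = Φ(0.5 × √31.5 − 1.96) = Φ(0.85) ≈ 80%. Total 126; 126/0.8 = 157.5, so 158 after dropout.
- g = d = 0.8: 15.70/0.64 = 24.5, so 25 per arm and power about 81%. Total 50; 50/0.8 = 62.5, so 63 after dropout.

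The formula therefore gives about 80% if the pilot estimate equals the truth.

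**2. Precision of the planning value.** SE(g) ≈ √(2/12 + g²/48). At g = 0.5 this is √(0.1667 + 0.0052) = 0.41. The 95% CI is 0.5 ± 1.96 × 0.4146, or −0.31 to 1.31. At g = 0.8 it is −0.03 to 1.63.

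**3. What errors within one SE do, with true d = 0.5** (normal approximation).

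| Observed g | n per arm | True power |
|---|---|---|
| 0.3 | 174.4 → 175 | Φ(4.68 − 1.96) ≈ 99.7% |
| 0.5 | 63 | ≈ 80% |
| 0.7 | 32.04 → 33 | Φ(2.03 − 1.96) ≈ 53% |
| 0.91 (one SE high) | 18.96 → 19 | Φ(1.54 − 1.96) ≈ 34% |

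**4. The whole rule.** For each scenario 200,000 pilots were simulated. g was drawn from the noncentral t distribution with the Hedges factor, n was taken from step 1 and rounded up, and power was evaluated at the true d (noncentral t below 200 per arm, normal above).

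| True d | Mean power, 12 per arm | Trials below 80% | Trials below 50% | Mean power, 9 complete cases per arm |
|---|---|---|---|---|
| 0.3 | 58% | 64% | 48% | 54% |
| 0.5 | 68% | 55% | 33% | 65% |
| 0.8 | 74% | 50% | 24% | 72% |

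Nine per arm is roughly what remains if 20% are lost, the limit set by the article's own follow-up goal. At true d = 1.0 with 12 per arm, mean power is still only 75%.

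**5. The alternative rule.** Fix the target difference Δ in advance and multiply the pilot SD by √(22/χ²₀.₂₀,₂₂) = 1.16, so n rises by 1.16² ≈ 1.35. If the true effect equals Δ, mean power is about 87% (standardised target 0.5 or 0.8). About 20% to 22% of pilots lead to power below 80%, and under 1% to power below 50%. With the pilot SD uninflated, mean power is 76% to 77%, so the gain in mean power comes from the inflation.

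**The case against.** The strongest reply is that every power figure is conditional on its planning value, that 80% is simply the input to a standard formula, and that the article offers only a recommendation. The later trial will have its own protocol, and its planners will see the reported confidence interval. Part of this stands. The text does not use the term point estimate; that is the plain reading, because the interval has no role in the rule. The reply does not rescue the rule, though. The rule chooses as its planning value a quantity with a standard error of about 0.41, and the article attaches the word minimum to the result and calls the future study fully powered.

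It is also fair that the simulated launch condition (g above 0) is not the article's own condition, which requires the observed difference to exceed the minimal important change. Applying such a threshold makes matters worse. With g of at least 0.5 as an illustration, mean power falls to about 45% at d = 0.5 and 66% at d = 0.8. A reader might take those as the plan's true figures. The article gives neither the minimal important change nor an SD, so they remain illustrative. Likewise, at d = 0.3 the true effect might be too small to matter, and the article does not let one settle that.

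A reader might also infer that small observed effects would lead to no trial because the required size is impractical. The article sets no such ceiling.

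**Conclusion.** The concern holds. The rule does not deliver a minimum of 80% power. Under the stated assumptions, mean true power is about 58% to 74% over true d of 0.3 to 0.8, and about 64% to 50% of the resulting trials fall below 80%. The direction is secure across the effects and pilot sizes tried; the amount depends on the unknown true d.

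Two stronger readings go too far. One is that the future trial will be underpowered: at d of 0.8 to 1.0, about half of pilots still lead to 80% or more, so what fails is the guarantee, not every realisation. The other is that the pilot is compromised: its conduct and its feasibility goals for recruitment, adherence and follow-up, which are reported descriptively, are unaffected. The point should be corrected, and it concerns one listed product of the pilot.

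**What to change.** In *Sample-size calculation* and *Statistical analysis*:
- Size the full-scale trial for a between-group difference fixed in advance as worthwhile for the chosen outcome, for example anchored on the minimal important change that *Primary outcome measure* already invokes.
- Take only the SD and retention from the pilot, using the upper one-sided 80% confidence limit of the SD (× 1.16 at 22 df; × 1.20 at 16 df if 9 per arm complete).
- Report the pilot effect size and its 95% CI descriptively only.
- State that the 80% power is conditional on the fixed difference.

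This is no guarantee either. The 87% in step 5 applies only if the true effect equals the target. With a standardised target of 0.5 and a true effect of 0.3, mean power is about 49%. The advantage is that the power then refers to a difference chosen for its relevance and not to a noisy estimate.

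If the observed effect is kept as the input, delete the words *a minimum of* and *fully powered*, and say that the 80% holds only if the true effect equals the pilot estimate. An expected power cannot be given in their place, because it depends on the unknown true effect.

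The cost is a few sentences of text, with no change to the pilot's size or conduct, and about 35% more patients in the future trial than the pilot SD alone would give.
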